### Planned statistical analysis

The primary objective of this study is to compare the rate of SREs from the date of randomization to mortality or 1 year, whichever occurs first, between participants receiving standard of care therapies versus participants receiving palliative RT for high-risk spine metastases. It is expected that nearly 60% of the enrolled participants will have at least 1 year of follow-up. The primary endpoint, SRE, has been previously defined as a composite measure including pathological spine fractures, spinal cord compression, or need of spinal interventions (palliative RT, or orthopedic surgery). SRE is a binary variable, with the rate of SRE defined as the number of lesions having SRE divided by the total number of eligible spine lesions. Given that this analysis is lesion-based, not participant-based, therefore, occurrence or non-occurrence at one lesion does not impact the status of other lesions in the same participant. Around 15% of participants may have multiple lesions, for which each lesion gets evaluated as an independent unit of analysis. Meanwhile, unlike the primary objective, the secondary objectives will be evaluated per participant.

A Wilcoxon rank-sum test will be utilized to compare the number of hospitalizations secondary to SREs between the trial arms. For comparing the quality of life and pain level between the trial arms, we will assess at 3 months, 6 months, 12 months, and within 1 week of any SRE (optional). The individual and overall scores derived from the scales described previously will be summarized at these assessment points using means and standard deviations, or medians, and inter-quartile ranges. We will evaluate categorical variables from EQ-5D-5L between the trial arms using Fisher’s test at each time point as well, from which we will determine odds ratios with 95% confidence intervals. We will summarize other non-quantifiable answers (such as treatment received for pain control) in a descriptive fashion. For the score for pain interference on the BPI Short Form scale, we will consider it as the average of the seven interference questions as long as ≥ 4 questions are complete. The mean difference between the trial arms with regard to scores on these scales will be assessed for both statistical and clinical significance. This will be done using Wilcoxon rank-sum tests and established MCIDs. For scales lacking established MCIDs, the “half standard deviation” rule will be applied, wherein the differences of a half standard deviation in the scores between trial arms considered clinically meaningful. After the study is completed, we will plot data at each assessment point, including the number of trial participants in each arm, mean scale scores, and their trends over time. Based on this, we will consider utilizing more exhaustive regression analyses including generalized linear models. We will utilize log-rank tests to compare time-to-event endpoints such as PFS and OS. For toxicity, we will tabulate all AEs at 3, 6, 12, and 24 months post-randomizations in the early upfront RT arm.

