Early palliative treatment has been demonstrated to improve the quality of life and even survival for patients with metastatic cancer [6]. Many specialized centers now advocate for earlier integration of RT in a patient’s treatment course, especially with patients living longer with their systemic disease. While several RCTs have evaluated the efficacy and safety of varying RT regimens for managing symptomatic bone lesions, few studies so far have examined the utility of early, upfront RT for the treatment of asymptomatic or minimally symptomatic spine metastases. It is however known that RT can significantly reduce the risk of SREs in patients with solid tumors metastasizing to the bone [14]. A phase 2, multicenter randomized controlled trial recently evaluated the role of early prophylactic RT in patients with high-risk bone metastases, including spine metastases, in patients with polymetastatic disease [14]. In this study, 78 patients with 122 high-risk bone metastases were enrolled and randomized to systemic therapy or observation, in addition to early prophylactic RT. At 1 year, SREs occurred in 1 of 62 lesions (1.6%) in the RT arm and 14 of 49 lesions (29%) in the standard-of-care systemic therapy arm (*P* < 0.001). Specific high-risk features were associated with a significant difference in the time-to-SRE, with most SREs seen in junctional or bulky (> 2 cm) spine disease (*P* = 0.016). Given this intriguing signal, the primary aim of the current randomized trial is to determine whether upfront, early palliative or pre-emptive RT, compared to standard-of-care systemic therapy in patients with high-risk asymptomatic or minimally symptomatic (non-opioid dependent) spine metastases leads to fewer SREs.

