### Power calculation

Power calculation has been performed by a formally trained institutional biostatistician, based on the primary endpoint of the rate of SREs from the date of participant randomization to their death or 12 months follow-up, whichever occurs first, in the two trial arms. SRE, a composite outcome measure, has been defined as a pathological spine fracture, spinal cord compression, or warranting of a procedure (palliative RT, interventional procedures, or spine surgery). SRE is a binary variable, where the event rate may be defined as the number of spine lesions with SRE occurrence divided by the total number of target spine lesions identified. Given the lesion-based analysis in the current trial, occurrence or non-occurrence of an SRE at one vertebra does not impact the status of other spine lesions within the same individual.

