Based on institutional records and previous trials, it is estimated that nearly 60–80% of patients may be successfully followed up for at least 1 year. For the standard of care trial arm, where only routine medical management is done, the rate of SRE is known to be nearly 60% within 1 year. Meanwhile, it is known that approximately three fourths of inpatient radiation consultations for painful bone metastases have been reported to lead to palliative RT. Furthermore, prior studies indicate that nearly 60% of RT-targeted spine lesions had been diagnosed ≥ 4 months prior to RT [7]. Therefore, we believe a 60% estimated event rate (as defined above) at 1 year is a conservative estimate. For the investigational trial arm, where early prophylactic RT is being provided to high-risk spine metastases, an SRE rate of 30% is estimated. The efficacy of RT in controlling pain from spine metastases is well-known. Since RT targets and mitigates, to a certain extent, the pathologic effect of a spinal metastases, this leads to reduced development of major bony pain, which is often a causative factor for SREs. For these SRE rates, inclusion of at least 66 individuals with evaluable SRE endpoints in a 1:1 randomization will allow the trial to achieve > 80% power based on a one-sided, two-sample proportion test with significance level of 0.05. Given that the individuals who withdraw prior to the SRE endpoint occurring may not evaluated as per the trial plan; therefore, a per-protocol analysis will be carried out. The limitations of the per-protocol analysis are mitigated by the use of hard endpoints in the current study along with the high morbidity and dismal prognosis of the participants. In order to ensure a minimum of 33 participants are enrolled per trial arm, we plan to over-accrue by 10%, so that the trial is sufficiently powered for the primary endpoint, resulting in a planned sample size of *N* = 74 participants. Additionally, we note that the unit of analysis is the spine lesion, and a small subset of patients may have multiple evaluable lesions (SREs). Since each lesion will be included separately in the analysis, therefore, the final sample size for the primary endpoint may be higher than estimated. We expect to enroll all 74 participants within 2 years.

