### Randomization, blinding, and allocation concealment

Participants are randomized to either the standard of care (arm 1) or early, upfront RT plus standard of care (arm 2). At the time of randomization, clinicians fill out the Lesion Identification Worksheet (Supplementary file 2: Appendix 2) to document the ≤ 5 high-risk spine metastases per protocol definition to be followed during the protocol in both arms. Once the participant’s eligibility is established, the registration is finalized, and the participants are randomized by the statistician for the study. Randomization is accomplished by the method of a random permuted block and stratified by disease histology (breast and prostate vs. other solid tumors) and planned standard of care treatment (observation vs. systemic therapy). After the treatment arm is determined by randomization, the research coordinator notifies the investigator of the treatment arm within 24 h of randomization. We employ allocation concealment by hiding the allocation sequence from which participants are assigned to the groups until the assignment to prevent selection bias. Both the treating physician and the participant are informed about the treatment they are receiving.

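### The primary SRE comparison treats several lesions from one randomised patient as independent, so its one-sided type I error can exceed 0.05

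*Protocol article*

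**What the plan says.** The unit of randomisation is the patient: "Participants are randomized to either the standard of care (arm 1) or early, upfront RT plus standard of care (arm 2"). At randomisation a worksheet records the "≤ 5 high-risk spine metastases per protocol definition to be followed during the protocol in both arms" (Randomization, blinding, and allocation concealment).

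The primary rate is the number of lesions with an SRE divided by the number of eligible lesions. The Planned statistical analysis section states: "Around 15% of participants may have multiple lesions, for which each lesion gets evaluated as an independent unit of analysis". It adds that "occurrence or non-occurrence at one lesion does not impact the status of other lesions in the same participant", and the Power calculation section has nearly the same sentence: "occurrence or non-occurrence of an SRE at one vertebra does not impact the status of other spine lesions within the same individual". The Power calculation section then draws a consequence for size: "Since each lesion will be included separately in the analysis, therefore, the final sample size for the primary endpoint may be higher than estimated".

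The only test named for this endpoint is a two-sample proportion test. The Abstract names it without sidedness. The Power calculation section makes it one-sided at 0.05, with 60% against 30% and at least 66 evaluable individuals. The Planned statistical analysis section names no primary test. Secondary objectives are evaluated per participant. The generalised linear models mentioned there are a possible later step for the scale scores, not for SREs.

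**The concern.** Choosing the lesion as the unit of analysis does not make lesions statistically independent. Even if an event at one vertebra never causes an event at another, outcomes in one patient are linked by shared causes. The protocol itself points to several:

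- Histology and planned standard treatment are stratification factors, and both are constant within a patient.
- The observation window closes at death for all of a patient's lesions together.
- Withdrawal removes the whole patient from evaluation.

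If that correlation is positive, the effective number of observations lies below the lesion count. A test that ignores this has too small a standard error and too narrow a confidence interval, and a positive result is then more likely by chance than the stated 0.05. This is the sole primary comparison of a small, open-label trial with a one-sided test.

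This is not a detail left to a statistical analysis plan. The protocol specifies independence outright, so an analysis plan that clustered on patient would contradict it.

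**Working it through.** **1. The plan's own figure.** Inputs from the Power calculation section: 0.60 against 0.30, one-sided 0.05, 80% power. With pooled variance and no continuity correction,

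n per arm = [1.645·√(2·0.45·0.55) + 0.842·√(0.60·0.40 + 0.30·0.70)]² / 0.30² = 32.9, so 33 per arm and 66 in total, with power 80.1%. Then 66/0.9 = 73.3, so 74. The stated figures reproduce, and they are counted in patients.

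**2. Design effect.** Let m be the number of lesions per patient and ρ the within-patient correlation (ICC). For a lesion-level rate with every lesion weighted equally,

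DEFF = 1 + (E[m²]/E[m] − 1)·ρ, and the true one-sided error is 1 − Φ(1.645/√DEFF).

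The 15% comes from the protocol ("Around 15% of participants may have multiple lesions") and the cap of 5 from the worksheet rule. The protocol gives neither ρ nor the distribution of m, so both are assumptions.

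- 2 lesions each: E[m] = 0.85 + 0.15·2 = 1.15; E[m²] = 0.85 + 0.15·4 = 1.45; ratio 1.261.
- 2 to 5, uniform: E[m] = 0.85 + 0.15·3.5 = 1.375; E[m²] = 0.85 + 0.15·13.5 = 2.875; ratio 2.091.
- 5 each: E[m] = 0.85 + 0.15·5 = 1.60; E[m²] = 0.85 + 0.15·25 = 4.60; ratio 2.875.

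| Lesions in the 15% | Lesions per arm (33·E[m]) | DEFF at ρ = 0.1 / 0.3 / 0.5 | True error by formula | Simulated range, ρ 0.1–0.5 |
|---|---|---|---|---|
| 2 each | 37.9 | 1.03 / 1.08 / 1.13 | 5.2 / 5.7 / 6.1% | 5.3–6.4% |
| 2–5, uniform | 45.4 | 1.11 / 1.33 / 1.55 | 5.9 / 7.7 / 9.3% | 5.8–9.3% |
| 5 each | 52.8 | 1.19 / 1.56 / 1.94 | 6.6 / 9.4 / 11.9% | 6.7–11.9% |

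The simulation is beta-binomial with 33 patients per arm, null rates of 45% and 60%, and the unclustered pooled z-test. At ρ = 0 the error is about 5% in every mix.

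**3. Precision and the lesion credit.** In the 2–5 uniform mix the 45.4 lesions per arm suggest 90% power. Divided by DEFF they are worth about 41, 34 and 29 independent lesions at ρ = 0.1, 0.3 and 0.5. The unclustered standard error is too small by 1 − 1/√DEFF, or about 5%, 13% and 20%.

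**4. Is 15% with few lesions realistic?** The earlier trial in the Background reports that "78 patients with 122 high-risk bone metastases were enrolled", or 122/78 = 1.56 per patient. With only 15% having several, that mean would need (1.56 − 0.85)/0.15, about 4.8 lesions in each of them. An assumed mix with mean 1.56 gives errors of 5.8, 7.4 and 8.9% at ρ = 0.1, 0.3 and 0.5. That trial counted all bone sites, so this is weak evidence for spine lesions.

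**5. Does the patient count survive?** If clustered data are weighted for their correlation, a patient with m lesions contributes m/(1 + (m − 1)ρ) effective lesions, which is never less than 1. For the worst case above (5 each, ρ = 0.5) this is 5/3 = 1.67, so 33·(0.85 + 0.15·1.67) = 36.3 per arm, above the 33 required. Equal weighting of lesions would instead leave 52.8/1.94 = 27.3 and about 73% power.

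**The case against.** The strongest objections concern size and certainty.

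- **The correlation is unknown.** A reader might infer that the type I error does exceed 0.05. The documents do not support that, because they give no correlation and at zero the test holds its level. What stands is that it can exceed 0.05, and does if the correlation is positive.
- **Five is a cap, not a typical number.** The protocol speaks of a small subset of patients. If affected patients mostly have 2 lesions, the excess is about one percentage point or less. A claim that a few patients with 5 lesions would drive the result goes beyond the text.
- **The sample size was not built on lesions.** A reader might infer that the trial is undersized. It is sized on 66 individuals, and no extra lesion is needed to reach 66 or 74. Only the added credit for further lesions is overstated.
- **The analysis test is inferred.** The proportion test is named for power, not in the analysis section. The inference is reasonable, given that the lesion is called an independent unit, but it remains an inference.
- **The non-impact sentences may be a scoring rule.** Read as saying that an event at one lesion is not scored against another, they are unobjectionable. That reading does not cover the explicit statement of independence or the sample-size credit.
- **Some sources of correlation are not documented.** Nothing states that one radiation field or operation covers several target lesions, and imaging times are the same for all participants. The argument does not need either.

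**Conclusion.** The point stands in conditional form: the protocol randomises patients, fixes lesions as independent units and credits extra lesions as sample size. This is wrong as written.

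With 15% of patients having several lesions and a correlation of 0.1 to 0.5, the one-sided error ranges from about 5.3% to 11.9% against a nominal 5%, depending mainly on how many lesions those patients have. The low end is minor; the high end more than doubles the stated risk. These figures rest on an assumed correlation, assumed lesion distributions and the inference that the proportion test is the analysis test.

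The defect lies in the test, its interval and the lesion credit. It does not lie in the planned enrolment or in the stated 80% power, which is a per-patient figure and reproduces.

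**What to change.** - Keep the binary lesion-level 12-month SRE rate as the primary endpoint. A time-to-event analysis would change the endpoint and is not needed.
- Replace the independent-lesion comparison with one that clusters on patient and uses a small-sample correction. One example is binomial GEE for the risk difference with an exchangeable working correlation, a bias-corrected robust standard error and a t reference; another is a Rao–Scott type test. The correction matters with 33 patients per arm, since an uncorrected robust standard error still gave about 5.2–6.5% in simulation.
- Add a per-patient analysis (any SRE among target lesions) as a sensitivity analysis.
- Delete the statement that separate counting of lesions may raise the sample size, and remove the word independent from the description of the unit of analysis.

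The cost is analysis wording and somewhat wider confidence intervals. No patients, visits or data are added, and 66 and 74 stay as they are. The change should be made before outcome data are analysed.

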EuroQoL 5-Dimensions (EQ-5D) is a widely utilized family of patient-reported instruments designed to capture and value health. These five dimensions are mobility, self-care, usual activities, pain/discomfort, and anxiety/depression. EQ-5D’s use as an outcome measure is recommended by several health technology assessment authorities [24, 25]. The 3-level EQ-5D (EQ-5D-3L) asks individuals to rate each of the five dimensions across three levels, while the EQ-5D-5L, introduced in 2009, does this for five levels [24, 26]. Whereas the FACT-G is a cancer-specific instrument, the EQ-5D is a two-part, generic preference-based outcome measure.

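### Fisher's test is a poor match for the ordered five-level EQ-5D-5L items: it ignores their order and gives no single odds ratio without a cut

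*Protocol article*

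**What the plan says.** The Protocol article, Study endpoints, lists health-related quality of life by FACT-G and EQ-5D-5L among the secondary endpoints. Rationale for study instruments and endpoints describes the instrument: "These five dimensions are mobility, self-care, usual activities, pain/discomfort, and anxiety/depression". The three-level version rates each dimension on three levels, "while the EQ-5D-5L, introduced in 2009, does this for five levels".

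Three statements in Planned statistical analysis bear on how these items are compared:

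- Summaries: "The individual and overall scores derived from the scales described previously will be summarized at these assessment points".
- The test for the categorical items: "We will evaluate categorical variables from EQ-5D-5L between the trial arms using Fisher’s test at each time point as well". The same sentence then names the estimate to be taken from this test: "from which we will determine odds ratios with 95% confidence intervals". No cut and no reference level is given.
- Differences in scale scores between the arms: "This will be done using Wilcoxon rank-sum tests and established MCIDs".

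Regression, including generalized linear models, is only to be considered once the data have been plotted at the end of the study. For the unit of analysis, "the secondary objectives will be evaluated per participant".

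**The concern.** The only categorical EQ-5D-5L variables that the document describes are the five dimension ratings, and each has five ordered levels. With two arms that makes a 2x5 table. Fisher's test on it treats the levels as unordered: exchanging the columns for no problems and extreme problems leaves the p-value unchanged. It also returns no single odds ratio. To obtain one, the analyst must cut the five levels into two groups, and a reference level would give four odds ratios instead of one. So the test and the estimate named in one sentence do not fit the variable they are applied to, and either repair loses the ordering.

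At stake are the odds ratios for mobility, pain/discomfort and the other dimensions. They are the only EQ-5D-5L effect measure for which the section names a confidence interval. The groups are small, and both the treating physician and the participant know the arm (Randomization, blinding, and allocation concealment).

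**Working it through.** **Arm sizes, from the document.** The plan states no power for the EQ-5D-5L. Its only power figure concerns the primary endpoint: "inclusion of at least 66 individuals with evaluable SRE endpoints in a 1:1 randomization". With rates of 60% and 30%, one-sided 0.05 and 80% power, the mean rate is 0.45 and

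n = [1.645·√(2·0.45·0.55) + 0.842·√(0.60·0.40 + 0.30·0.70)]² / 0.30² = (1.157 + 0.565)² / 0.09 ≈ 32.9, so 33 per arm.

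Then 66/0.90 = 73.3, so 74 enrolled. Both stated figures reproduce. This gives 37 per arm enrolled, 33 evaluable, and about 0.60 × 37 ≈ 22 per arm with one year of follow-up, using the 60% in Planned statistical analysis.

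**Assumptions, not from the document.** One five-level item; two-sided 0.05; a common cumulative odds ratio (OR) of 2, 3 or 4. Control distributions, in percent from best to worst level: 20/20/20/20/20, 30/30/25/10/5, 10/25/35/20/10 and 50/25/15/7/3. There were 800 simulated trials per scenario, so the standard error of a power is at most √(0.25/800) ≈ 1.8 points.

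**Shift.** If c is a control cumulative probability, the treated one is c′ = OR·c / (1 − c + OR·c). For 30/30/25/10/5 and OR 3, the cumulative 0.30, 0.60, 0.85, 0.95 become 0.563, 0.818, 0.944, 0.983.

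**Wilcoxon power minus 2x5 Fisher power, in points, range over the four distributions and three ORs:**

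| Per arm | Difference |
|---|---|
| 37 | 13 to 23 |
| 33 | 12 to 25 |
| 22 | 6 to 25 |

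By OR, over all three arm sizes, the difference is 6 to 17 at OR 2, 15 to 25 at OR 3 and 13 to 25 at OR 4. A separate run at 30 per arm with control 30/30/22/13/5 gave 64% against 43% at OR 3, 30% against 19% at OR 2, and 13% against 11% at OR 1.5.

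**Effect of a cut.** With 37 per arm, 30/30/25/10/5 and OR 3, Wilcoxon has 72% power and 2x5 Fisher 53%. The 2x2 Fisher test has 53%, 43%, 12% or 0.1% as the cut moves from after level 1 to after level 4. Exact binomial enumeration of the same four cuts gives 53%, 46%, 14% and 0.5%. Over all scenarios, the loss against Wilcoxon runs from about 7 points at the best cut to more than 80 at an extreme one.

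**Null.** Over the twelve null scenarios, mean rejection was 5.1% for Wilcoxon and 5.3% for 2x5 Fisher. The 2x2 Fisher test was conservative (0% to 4.8%).

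**Where proportional odds fails** (30 per arm, control 30/30/22/13/5, 1000 trials; shifts assumed):

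| Treated arm, % | Wilcoxon | 2x5 Fisher | OR by cut, after level 1, 2, 3, 4 |
|---|---|---|---|
| 55/5/22/13/5 | 20% | 64% | 2.85, 1.00, 1.00, 1.00 |
| 30/55/8/5/2 | 24% | 45% | 1.00, 3.78, 2.92, 2.58 |
| 50/10/10/20/10 | 7% | 56% | 2.33, 1.00, 0.51, 0.47 |

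The first entry, for example, is (0.55/0.45)/(0.30/0.70) = 2.85; one level further it is (0.60/0.40)/(0.60/0.40) = 1.00. So the power ranking can reverse, and the odds ratio from a cut can change from benefit to none, or to harm, on the same data. Under exact proportional odds the population odds ratio is the same at every cut, and only its sample estimate and precision vary.

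**The case against.** The strongest reply is that an order-respecting test is already planned. The section speaks of individual as well as overall scores, applies Wilcoxon tests to scores on the scales, and introduces Fisher's test as an addition. On that reading the items are tested by Wilcoxon too, and Fisher's test is a supplementary display. This stands in part. The text does not settle whether the items get the Wilcoxon test, so a reader who infers that the whole EQ-5D-5L comparison loses power goes further than the document allows. But the Wilcoxon test as planned gives no odds ratio, so the mismatch between Fisher's test and its odds ratio remains on either reading.

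Second, the cut may be stated in an analysis plan that is not shown. That is fair for the cut itself, and the document does not support an inference that it will be chosen after the data are seen. The choice of Fisher's test for an ordered item, however, is fixed here, and a stated cut would still discard the ordering.

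Third, the power loss rests on a model that favours the ordinal test. This also stands: every effect and distribution is assumed, and the ranking reverses in the last table. Those reversals need an effect confined to one step of the scale or a shift in opposite directions, which an ordered improvement would rarely produce.

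Fourth, Fisher's test is valid at these sizes and needs no proportional-odds assumption. That is correct; the point concerns efficiency and interpretation.

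**Conclusion.** The point holds in a limited form. Fisher's test on a five-level EQ-5D-5L item ignores the order of the levels and cannot supply the single odds ratio that the plan asks of it. Cutting to two groups supplies one at the cost of information, with power and estimate depending on the cut.

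The size is conditional: roughly 6 to 25 points of power for the 2x5 test under proportional-odds shifts with OR 2 to 4 and 22 to 37 per arm, and less for smaller effects. A reader might take some figure in that range as a fixed loss in this trial. The document gives no EQ-5D-5L effect, distribution or power claim from which one could be derived. Nor does anything here suggest false-positive results. The trial is powered on skeletal-related events alone, so this is a minor improvement to one secondary endpoint.

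**What to change.** In Planned statistical analysis, replace Fisher's test for the EQ-5D-5L dimensions with a proportional-odds (ordinal logistic) model on all five levels at each time point, with arm as covariate, and report the common odds ratio with its 95% confidence interval. This delivers the estimate that the plan already wants, and the model's unadjusted score test is the Wilcoxon rank-sum test already named in the section. Check the proportional-odds assumption; where it is doubtful, report the Wilcoxon-Mann-Whitney probability with its 95% confidence interval. Keep Fisher's test for binary or unordered variables only.

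The cost is about one sentence, with no new data, visits or participants. Ethical considerations, monitoring, and data confidentiality says that outcomes will not be reviewed early, so the change can be made before results are known. The downside is that a common odds ratio relies on proportional odds, and the Wilcoxon fallback has low power against the irregular shifts shown above.
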